**1.5 years**

**c.** What is the total amount of time each participant will be involved?

**8 weeks**

**d.** If different phases are involved, what is the duration of each phase in which the participants will be involved? If no phases are involved, enter "not applicable."

**Not applicable**

**e.** List the procedures, the length of time each will take, and the frequency of repetition, and indicate whether each is done solely for research or would already be performed for treatment or diagnostic purposes (routine care) for the population. *Insert additional table rows as needed.*

| Procedure | Length of Time Required of Participants | Frequency of Repetition | Research (Res) –OR- Routine Care |
| --- | --- | --- | --- |
| **Telephone screening** | **15 minutes** | **Once** | Res Routine |
| **Final screening** | **30 minutes** | **Once** | Res Routine |
| **Testing visit 1** | **3.5 hours** | **Twice** | Res Routine |
| **Testing visit 2** | **45 minutes** | **Twice** | Res Routine |
| **Testing visit 3** | **15 minutes** | **Twice** | Res Routine |
| **Clinic visit for HIIT** | **20 minutes** | **18** | Res Routine |
| **Clinic visit for MIT** | **60 minutes** | **30** | Res Routine |

**f.** Will an interview script or questionnaire be used? Yes No

**If Yes**, attach a copy.

**g.** Will participants incur any costs as a result of their participation? Yes No

**If Yes**, describe the reason for and amount of each foreseeable cost.

**h.** Will participants be compensated? Yes No

**If Yes**, complete i-v:

**i.** Type: (e.g., cash, check, gift card, merchandise):**check**

**ii.** Amount or Value: **$600**

**iii.** Method (e.g., mail, at visit): **at visit**

**iv.** Timing of Payments: (e.g., every visit, each month):**$100 after baseline testing; $500 after final testing.**

**v.** Maximum Amount of Payments per Participant:**$600**

**17. Describe the potential benefits of the research.**

**The health benefits of regular exercise are well established. And yet it remains difficult for many persons to find the time and circumstances that lead to engaging in regular exercise of a magnitude and duration generally believed to convey health benefits. Therefore, it is essential to develop novel strategies to help people achieve these goals. Here we propose a time-efficient exercise alternative to reduce the risk of comorbidities associated with adiposity while making adherence easier.**

**18. Risks**

**a.** List the known risks—physical, psychological, social, economic, and/or legal—that participants may encounter as a result of procedures required in this protocol. Do not list risks resulting from standard-of-care procedures. *Note. Risks included in this protocol document should be included in the written consent document.*

**Physical risks include possible adverse reaction to the blood draws. These can include lightheadedness or fainting, along with pain, bruising, or infection at the injection site. During the VO2 Maximum testing there is a rare risk of ischemia or cardiac arrest. During the Wingate Power Test and the exercise training protocol, there is a potential risk of mild muscle soreness, an arrhythmia and fatigue.**

**b.** Estimate the frequency, severity, and reversibility of each risk listed.

**We expect adverse reactions to the blood draws to be rare, not severe, and completely reversible. Any soreness or fatigue related to exercise is not expected to be severe and is also completely reversible.**

**c.** Is this a therapeutic study or intervention? Yes No

**If Yes**, complete the following items:

**i.** Describe the standard of care in the setting where the research will be conducted: **The standard of care for increased fitness in overweight and mildly obese persons is exercise prescription.**

**ii.** Describe any other alternative treatments or interventions: **There are a myriad of exercise modes and programs for persons desiring greater physical fitness and health outcomes.**

**iii.** Describe any withholding of, delay in, or washout period for standard of care or alternative treatment that participants may be currently using: **None. All participants will be exercising.**

**d.** Do you foresee that participants might need additional medical or psychological resources as a result of the research procedures/interventions? Yes No

**If Yes**, describe the provisions that have been made to make these resources available.

**e.** Do the benefits or knowledge to be gained outweigh the risks to participants?

Yes No

**If No,** provide justification for performing the research:

**19. Precautions/Minimization of Risks**

**a.** Describe precautions that will be taken to avoid risks and the means for monitoring to detect risks.

**To prevent risks associated with the blood draws experienced phlebotomists, strict sterile technique, and applying pressure on the injection site will be utilized to minimize pain, infection, and bruising. Participants will be closely monitored during blood draws, and at the first sign of lightheadedness, clamminess, or fainting, they will be placed in a reclined position with legs elevated, and pulse and blood pressure will be assessed until they have recovered fully. To avoid exercise-related risks, all study personnel related to the exercise protocol are exercise physiologists, CPR and defibrillator certified. Subjects will be instructed in technique to avoid injury and minimize soreness. Subjects will be supervised during on-site exercise training.**

**If study involves drugs or devices skip Items 19.b. and 19.c., go to Item 20, and complete the** [**Drug**](http://www.uab.edu/irb/forms/drug-review-sheet.doc) **or** [**Device**](http://www.uab.edu/irb/forms/device-review-sheet.doc) **Review Sheet, as applicable.**

**b.** If hazards to an individual participant occur, describe (i) the criteria that will be used to decide whether that participant should be removed from the study; (ii) the procedure for removing such participants when necessary to protect their rights and welfare; and (iii) any special procedures, precautions, or follow-up that will be used to ensure the safety of other currently enrolled participants.

**(i) Any participant experiencing a documented injury or other physical condition, the participant and the study coordinator can assess the situation and determine if the participant wishes to continue. If symptoms do not improve, the participant will be removed from the intervention. (ii) Participants requiring removal from the study will be notified promptly and instructed to discontinue the intervention (exercise). Referral to their primary care provider will be made if necessary, and the participant will be provided with results of any tests or measurements that are available as a result of their participation in the study. (iii) All currently enrolled participants will be continually monitored for adverse reactions or other problems.**

**c.** If hazards occur that might make the risks of participation outweigh the benefits for all participants, describe (i) the criteria that will be used to stop or end the entire study and (ii) any special procedures, precautions, or follow-up that will be used to ensure the safety of currently enrolled participants.

**(i) If a significant percentage of participants (at least 10%) of participants experience a serious adverse event, the study would be stopped. (ii) If the study were to be stopped, all currently enrolled participants would be contacted by telephone promptly and assessed for adverse reactions, as well as be scheduled for a final clinic visit for further assessment.**

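### Item 19.b(i) lets a participant return to hard exercise without medical review after a suspected arrhythmia or ischemic symptom that has settled

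*Protocol*

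**What the plan says.** Item 19.b of the protocol asks for the criteria for taking an individual out of the study. The reply in part (i) covers any recorded injury or other physical problem with a single rule: "the participant and the study coordinator can assess the situation and determine if the participant wishes to continue". It adds one compulsory trigger: "If symptoms do not improve, the participant will be removed from the intervention".

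Part (ii) describes what happens to participants who are being removed, and says "Referral to their primary care provider will be made if necessary". Part (iii) says "All currently enrolled participants will be continually monitored for adverse reactions or other problems".

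Item 18.a names the exercise hazards. On fitness testing: "During the VO2 Maximum testing there is a rare risk of ischemia or cardiac arrest". On the power test and training: "During the Wingate Power Test and the exercise training protocol, there is a potential risk of mild muscle soreness, an arrhythmia and fatigue".

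Item 19.a prescribes a response to one type of event, during blood draws: "at the first sign of lightheadedness, clamminess, or fainting, they will be placed in a reclined position with legs elevated". For exercise it describes instruction in technique, supervised on-site sessions, and staff who are exercise physiologists trained in CPR and defibrillation.

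**The concern.** The rule in 19.b(i) is built around whether symptoms get better and whether the participant wants to go on. That suits soreness, fatigue and minor injury. It suits an arrhythmia or an ischemic symptom brought on by effort badly. Such a symptom may disappear when the effort stops, and its disappearance says little about the next maximal or interval bout. Item 14 describes HIIT as repeated efforts above 90% of VO2max.

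The stake is participant safety, not bias in an estimate. 19.b(i) is the only individual removal criterion in the protocol. Followed as written, it can put a participant with a recent cardiac symptom back into hard exercise on his own wish and a coordinator's assessment. His wish is also a weak safeguard: under item 16.h, $500 of the $600 payment comes only after final testing, and participants are 17 to 19 years old.

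**Working it through.** There is no plan figure to reproduce. The check sets the provisions side by side and asks whether any of them requires medical review before exercise resumes.

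**Step 1: apply 19.b(i) to the listed risks.** Take a suspected arrhythmia in training, or an ischemic symptom at VO2 maximum testing, that settles with rest. The symptom has improved, so the compulsory trigger is not met. What remains is the joint assessment and the participant's wish. No clinician appears in the rule.

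**Step 2: look for the missing step elsewhere.**

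| Provision | What it supplies | Medical clearance to return? |
|---|---|---|
| 15, exclusion criteria | Diagnosed heart conditions and PARQ, at entry | No; acts before training starts |
| 19.a | Supervised on-site training, CPR- and defibrillator-certified staff | No; emergency response |
| 19.b(ii) | Primary care referral, at discretion | No; only for those being removed |
| 19.b(iii) | General monitoring | No |
| 19.c | Stops the study if at least 10% have a serious adverse event | No; a study-level rule |
| 2.f and 18.d | Medical supervision; extra medical resources | Answers unreadable; neither changes the text of 19.b(i) |

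On 19.c: 10% of 36 is 3.6, so four participants would be needed. It cannot govern one person's return.

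**Step 3: is a later maximal test in prospect?** Item 13 places cardiovascular fitness at baseline and 6 weeks, and item 16.e repeats each testing visit. A final VO2 maximum test is therefore a fair inference, although it is not named as such. The point stands on training alone. Mandatory removal is also only from the intervention, so 19.b does not expressly keep a removed participant out of that test.

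**Step 4: cost of a clearance step.** Item 16.a puts the training period at Day 1 to Day 42, which is 6 weeks. Item 16.e gives 18 HIIT visits and 30 MIT visits.

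- Sessions per week: HIIT 18 / 6 = 3; MIT 30 / 6 = 5.
- Assumed wait of 1 week: 3 / 18 = 17%; 5 / 30 = 17%.
- Assumed wait of 2 weeks: 6 / 18 = 33%; 10 / 30 = 33%.

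These are shares of sessions missed by one affected participant. The waiting time is an assumption, because the protocol gives none. No event rate is assumed.

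**The case against.** The strongest objection is that the decisive answer may be hidden. Item 2.f asks whether medical supervision is needed and who provides it, and the tick is lost. If a supervisor is named, he or she may cover the whole study, and 19.b(i) need not say so again. Item 18.d ("Do you foresee that participants might need additional medical or psychological resources as a result of the research procedures/interventions") is unreadable in the same way. It follows that nobody may claim the study lacks medical supervision, and this point does not. But 19.b(i) states who assesses an event and what compels removal, and it sends no cardiac symptom to such a supervisor.

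Second, the rule is permissive. It does not order a return to exercise, and it forbids neither referral nor a stop by staff. Item 2.e also has the principal investigator personally involved in early testing and training sessions. A symptom that recurs on every effort could fairly be read as not improved. All of this stands and narrows the gap, chiefly to a first episode that resolves. It does not close the gap, because none of it is medical clearance.

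Third, this might be called a mere omission from a short ethics-board form. But the form asks for removal criteria, and the answer supplies a single criterion that fits two of the protocol's own listed risks poorly. That is a rule badly fixed rather than silence.

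Finally, chest pain and exertional syncope are not in the exercise risks of 18.a. They belong in the fix as ways in which the listed ischemia or arrhythmia may show itself, not as additional listed risks.

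**Conclusion.** The concern holds. As written, 19.b(i) requires no medical review after a suspected arrhythmia or ischemic symptom that improves, and no other readable provision requires it before exercise resumes. The amendment should be made.

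The size in events cannot be stated. Item 18.a says only that ischemia and cardiac arrest are rare and that arrhythmia is possible. Item 18.b, which asks for frequency and severity, answers only for blood draws, soreness and fatigue. Events should be uncommon among 36 generally healthy males aged 17-19 screened for diagnosed heart conditions and by PARQ. Cardiac arrest is outside the claim, and no effect on the trial's estimates is alleged.

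Confidence is medium, because the answer to 2.f is unreadable and the final VO2 maximum test is inferred.

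**What to change.** Amend 19.b(i) in two parts.

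1. Limit the present participant-and-coordinator rule to soreness, fatigue and minor injury.
2. For suspected arrhythmia, chest pain or another ischemic symptom, or exertional syncope, stop exercise at once. Allow further training or exercise testing, including the final VO2 maximum test, only after documented clearance by the participant's primary care provider or by the medical supervisor under 2.f, if one is named. Without clearance, withdraw the participant from the intervention and do not perform the maximal test.

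This is a new step, since 19.b(ii) offers referral only to those leaving. The amendment must say who arranges the clearance and where it is recorded.

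The cost falls on the affected participant alone: 3 to 6 HIIT sessions or 5 to 10 MIT sessions under the assumed 1 to 2 week wait. A participant who is not cleared loses the rest of the training and the final fitness measurement. In an arm of 18 that is 1 / 18 = 5.6% of the planned fitness data per such case.

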**13. Purpose—in nontechnical, lay language**

Summarize the purpose and objectives of this protocol, including any related projects, in one short paragraph.

This is a single site, 2 parallel arm, randomized, controlled trial comparing the effectiveness of a High Intensity Interval Training (HIIT) versus a continuous Moderate Intensity Training (MIT) program on cardiovascular and metabolic health outcomes in overweight adolescent males. The study will be conducted over a total of 8 weeks. 36 participants will be enrolled, with 18 randomized to HIIT and 18 randomized to MIT. Multiple measures will be performed at baseline and 6 weeks, including anthropometry, body composition, insulin sensitivity, cardiovascular fitness, free living physical activity, blood pressure, blood assays, and appetite sensations.

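### Item 19.b treats stopping exercise and leaving the study as one event, so participants removed for injury or symptoms could be lost before the only post-baseline outcome visit

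*Protocol*

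**What the plan says.** Protocol item 19.b(i) deals with a participant who has an injury or other physical condition: "If symptoms do not improve, the participant will be removed from the intervention". Item 19.b(ii), the procedure for carrying this out, changes the term: "Participants requiring removal from the study will be notified promptly and instructed to discontinue the intervention (exercise". The participant may then be referred to his primary care provider. On test results, the item says: "the participant will be provided with results of any tests or measurements that are available as a result of their participation in the study". No outcome visit is mentioned, and no route is described for stopping exercise while remaining in follow-up.

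Three other places bear on this:

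- Item 13 sets the outcome schedule: "Multiple measures will be performed at baseline and 6 weeks". No assessment is listed between these two time points.
- Item 19.c(ii) covers a stop of the whole study. Enrolled participants are telephoned, "as well as be scheduled for a final clinic visit for further assessment".
- Item 16.h.iv gives the payments, in dollars: "100 after baseline testing; $500 after final testing".

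**The concern.** The trial randomises 36 young men, 18 per arm, to compare the effectiveness of two exercise programs. There is one post-baseline time point, so anyone not measured at 6 weeks contributes no outcome. If a man who stops exercising is also taken off the study, his outcome is missing because of something that happened after randomisation and may be related to the program he was given.

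The programs are not alike in what they ask of participants. HIIT is 18 visits of 20 minutes at high intensity; MIT is 30 visits of 60 minutes at moderate intensity. Injury and persistent symptoms could plausibly arise at different rates. If those removed would also have changed less, or more, than those who stay, the men left at 6 weeks are no longer comparable by randomisation.

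This is not something to leave to a statistical analysis plan. Such a plan can define analysis sets and missing-data methods, but it cannot restore measurements that were never taken. The protocol determines who is invited to be measured.

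**Working it through.** **1. The passages side by side.**

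| Place | Event | Status given | Return visit mentioned |
|---|---|---|---|
| 19.b(i) | Symptoms do not improve | Out of the intervention | None |
| 19.b(ii) | Procedure for removal | Out of the study; stop exercise | None |
| 19.c(ii) | Whole study stopped | Study ends | Final clinic visit |

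Parts (i) and (ii) answer one question about one event but give two statuses. Under the first, the 6-week visits in items 13 and 16.e would still apply. Under the second, they would not.

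**2. Planned exposure** (item 16.e): HIIT 18 × 20 min = 360 min = 6 hours; MIT 30 × 60 min = 1,800 min = 30 hours.

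**3. Possible size of the bias.** The protocol gives no effect size, SD, removal rate or dropout allowance, so there is no planned figure to reproduce. What follows is an illustration.

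Inputs from the protocol: n = 18 per arm. Assumed: k, the number removed in an arm and not measured, and g, the mean outcome of those who stay minus the mean outcome of those removed, in SD units.

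Within one arm, the mean of all randomised is (1 − k/18) × M_stay + (k/18) × M_removed = M_stay − (k/18) × g. The stayers' mean is therefore off by (k/18) × g. For the difference between arms:

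bias = (k_H/18) × g_H − (k_M/18) × g_M

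| Removed in HIIT, MIT | g = 0 | g = 0.5 SD | g = 1 SD |
|---|---|---|---|
| 1, 0 | 0 | 0.028 | 0.056 |
| 2, 0 | 0 | 0.056 | 0.111 |
| 3, 0 | 0 | 0.083 | 0.167 |
| 4, 0 | 0 | 0.111 | 0.222 |
| 3, 1 | 0 | 0.056 | 0.111 |
| 2, 2 | 0 | 0 | 0 |

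The same g is used in both arms. Placing the one-sided removals in MIT instead reverses the sign.

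**4. Yardstick.** Standard error of the difference with everyone measured: √(1/18 + 1/18) = √(2/18) = 0.333 SD. The largest entry is 0.222/0.333 = 0.67 of a standard error. Three one-sided removals at a 1 SD gap give 0.167/0.333 = 0.50.

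**5. Precision.** With a two-sided 5% t-test (assumed), 18 v 18 has 80% power for a difference of 0.96 SD. At that difference, power is 78.8% with 17 v 18, 77.4% with 16 v 18, 75.9% with 15 v 18 and 74.2% with 14 v 18. The loss of power is modest; the main issue is possible bias.

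**The case against.** The strongest reply is that this is loose wording in an ethics form. The form's question itself asks for "the criteria that will be used to decide whether that participant should be removed from the study", so the answer borrows the phrase. The investigator's own criterion concerns the intervention, and the only instruction to the participant is to stop exercising. Items 13 and 16.e schedule testing at baseline and 6 weeks without restricting it to men who finish training. The return visit in 19.c(ii) answers a prompt about safety follow-up and is not shown to include the outcome measures. Item 18.b expects soreness and fatigue to be mild and reversible, so removals may be few.

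Much of this stands, and it rules out several stronger readings that a reader might infer:

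- **That removed participants are denied 6-week testing.** The document neither schedules nor forbids it for them; the inference rests on silence.
- **That a completers-only analysis is planned.** No analysis set is stated here, and that may properly sit in an analysis plan that is not shown.
- **That the bias is established, or favours a particular arm.** Item 19.b covers any injury or physical condition, not only harm from the assigned exercise, and no removal rates are given.
- **That the payment schedule encourages men to hide symptoms.** The $500 is tied to final testing, not to completing training, so it can equally encourage return. Nothing in the document shows concealment.

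The inconsistency itself remains. The form explains where one term came from, but the answer uses both terms for one event, and staff following part (ii) literally would discharge the participant before his outcome visit.

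**Conclusion.** The point holds as an inconsistency with a possible statistical consequence, not as a demonstrated bias. Items 19.b(i) and (ii) must be reconciled, because only one of the two statuses keeps the participant in line for the sole post-baseline measurement.

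Bias arises only if removals go unmeasured, those removed differ in outcome from those who stay, and the products of removal fraction and gap do not cancel between arms. Within the range illustrated it runs from nothing to 0.22 SD, or up to two thirds of a standard error. The upper end needs four removals, all in one arm, and a full 1 SD gap; none of these comes from the protocol. The case for acting is that outcomes not collected cannot be recovered later and the correction is small.

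**What to change.** In item 19.b, separate stopping exercise from leaving the study and use the two terms consistently. State that a participant who stops exercise remains enrolled and, if he agrees, is invited to the scheduled 6-week testing for those measures the investigators judge safe for him. In item 16.h, state that the $500 is paid for attending final testing whether or not training was completed. The rule for when exercise stops is not altered, and no view is taken on it.

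The cost is about one paragraph in each item. Item 16.e already lists each testing visit twice and item 16.h already sets a $600 maximum per participant, so no new visit or payment is created; no study budget is shown against which to check this further. The downside is slight dilution of the estimated effect by men who did not finish training.
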